### **9.2.3 Suspected unexpected serious adverse reactions (SUSARs)**

Not applicable.

## **9.3 Annual safety report**

Not applicable.

## **9.4 Follow-up of adverse events**

All AEs will be followed until they have abated, or until a stable situation has been reached. Depending on the event, follow up may require additional tests or medical procedures as indicated, and/or referral to the general physician or a medical specialist. SAEs need to be reported till end of study within the Netherlands, as defined in the protocol

## **9.5 Data Safety Monitoring Board (DSMB) / Safety Committee**

Not applicable

## 10. STATISTICAL ANALYSIS

### 10.1 Primary study parameter(s)

Objective 1: To investigate the tolerability and safety of HALF-MIS used in elderly patients with chronic musculoskeletal pain our primary study parameters are Safety (listing (S)AEs) and tolerability (UTAUT and ARTS). These parameters will be analyzed descriptively.

Objective 2: To investigate the effect on pain of HALF-MIS used in elderly patients with chronic musculoskeletal pain we use one primary endpoint: (self-reported Pain (NRS). Pain intensity will be analysed as appropriate depending on data distribution with a two-sided 0.05 level of significance (superiority in the Half-Miss group). Effect sizes and 95% confidence intervals will be calculated for the primary and secondary outcome measures. Changes within the treatment groups over time as well as differences between groups will be assessed by intention-to-treat analyses. Also the primary analysis will follow the per protocol principle. Sensitivity analyses will be provided to evaluate robustness of the results with regard to centre effects, HADS and/or pain medication.

Objective 3: To investigate the effect on central sensitization of HALF-MIS used in elderly patients with chronic musculoskeletal pain. The primary outcome measure is QST. We will compare outcomes before and after treatment by parametric (students t-test) or non-parametric (Mann-Whitney) tests.

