### 3. STUDY DESIGN

#### Study design

Placebo controlled pilot study in 60 patients with a chronic musculoskeletal pain syndrome. 30 patients per center will be recruited and screened through one of the participating centers: 1) University Hospital of Copenhagen, Denmark; 2) Anesthesiology Pain Center, University Medical Center Groningen, The Netherlands. The primary examination must result in a cumulated NRS score of more than 3. After randomization there will be a treatment and a control group.

Every patient in the treatment group will receive eight HALF-MIS treatments and the control group eight placebo treatments in three weeks. Every (placebo) treatment will be about 20 minutes and all patients in both groups will undergo all the measurements (NRS, CSI, EuroQol 5D-3L, HADS, PDI, QST, ARTS and UTAUT as described below).

For the recruitment procedure, see paragraph 11.2. The first visit concerns a screening visit for which participants will be invited to the research site at Beatrixoord. When eligible, their treatments will be scheduled. Relevant questionnaires will be sent before each visit. The QST measurements will take place before the first treatment session, after the last treatment session and six weeks after the last treatment session. These items will take about 25-30 minutes to be performed. For an overview of performed questionnaires/measurements see the flowchart at the end of this section.

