### 4.2 Inclusion criteria

In order to be eligible to participate in this study, a subject must meet all of the following criteria:

1. The symptoms of pain have been present for 3 months or more
2. The symptoms of pain are present every day with a minimum level of NRS=4 (Moderate and severe pain)
3. The symptoms of pain are resulting from a condition diagnosed as a musculoskeletal disease listed in the ICD-10 of the WHO M00-M99.9 (But NOT M50.0, M50.1, M51.0 and M51.1 that are Prolapsus Disci Intervertebralis with myelopathy/radiculopathies – as the pain syndrome in these cases are expected to be predominantly neurogenic)
4. Adequate communication and understanding of the language
5. Age ≥ 65 years
6. Available during the intervention.

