### 8.2 Randomisation, blinding and treatment allocation

#### Randomization

Randomization is secured by the drawing of lots consisting of closed envelopes containing information on whether the patient has been placed in the treatment or the placebo group, as well as an additional description of group definition and content. 30 patients per center are included with a disposition of the lots so that each center will include 15 patients in the treatment group and 15 patients in the control.

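### The primary pain comparison is not fixed: the test follows the observed distribution, no primary time is named, and centre is only a sensitivity item although allocation is balanced within centre

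*Protocol*

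**What the plan says.** For objective 2, section 10.1 commits to a single outcome ("we use one primary endpoint: (self-reported Pain (NRS") and then leaves the method open: "Pain intensity will be analysed as appropriate depending on data distribution with a two-sided 0.05 level of significance". A bracket after this ties the test to superiority of the active arm.

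On contrasts the section says: "Changes within the treatment groups over time as well as differences between groups will be assessed by intention-to-treat analyses". Neither contrast is called primary. Effect sizes with 95% confidence intervals are promised.

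On centre it says: "Sensitivity analyses will be provided to evaluate robustness of the results with regard to centre effects, HADS and/or pain medication". Section 8.2 (Randomization), however, builds centre into the allocation: "30 patients per center are included with a disposition of the lots so that each center will include 15 patients in the treatment group", with 15 controls per centre as well.

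On timing, the Summary has patients complete questionnaires at the first, last and follow-up visits. That gives one baseline and two post-baseline occasions. Section 8.1.1 lists NRS as the pain endpoint without a time, and section 10.1 adds none.

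Section 4.4 gives 30 patients per arm and states that no pilot data on pain exist. It offers no effect size, SD, power or correlation. Section 4.2 restricts entry: "The symptoms of pain are present every day with a minimum level of NRS=4".

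**The concern.** Section 10.1 attaches a 5% test to a single endpoint but leaves four things open that determine what the test means: the statistic, the time, the contrast and the role of centre.

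- **Statistic.** A t-test estimates a difference in means and a Mann-Whitney test compares ranks. If the distribution decides between them and no rule is stated, the promised effect size and interval are undefined until the data are in. That matters in a pilot whose results are meant to inform later trials (section 4.4).
- **Time.** Two post-baseline occasions can each be presented as the primary result.
- **Contrast.** Patients enter on a pain threshold, so some fall in NRS can be expected in both arms without any treatment effect. Within-arm change listed beside the randomised comparison, without a stated rank, can be read as efficacy.
- **Centre.** When allocation is balanced on a factor that the main analysis ignores, between-centre variation stays in the error term.

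With 60 patients and no replacement of withdrawals (section 8.5), precision is scarce. An analysis that uses baseline NRS and centre needs no further patients.

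**Working it through.** **1. The plan's own figure.** 2 centres × 15 = 30 per arm, 60 in total. Sections 4.4 and 8.2 agree. No power or effect size is given, so 30 per arm cannot be derived from a formula. What follows is about precision only.

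**2. Inputs.** From the protocol: n = 30 per arm, two-sided 0.05 (section 10.1), entry at NRS ≥ 4 (section 4.2). Assumed: unrestricted NRS with mean 5 and SD 2 at baseline, SD 2 for the outcome, correlation ρ = 0.3, 0.5 or 0.7, and a true difference of 1 point. The comparator is an unadjusted t-test on post-treatment scores.

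**3. Effect of the entry rule.** With a = (4 − 5)/2 = −0.5, λ = φ(a)/(1 − Φ(a)) = 0.509. The baseline variance kept among enrolled patients is k = 1 + aλ − λ² = 1 − 0.255 − 0.259 = 0.486.

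**4. Quantities among enrolled patients.**
- Outcome SD, unadjusted: 2√(ρ²k + 1 − ρ²)
- Residual SD with ANCOVA: 2√(1 − ρ²)
- Correlation ρ*, where ρ*² = ρ²k/(ρ²k + 1 − ρ²)
- Equivalent unadjusted N = 60/(1 − ρ*²)
- 95% CI half-width = t × SD × √(2/30)
- Power from the noncentral t with noncentrality 1/(SD√(2/30)), on 58 df unadjusted and 56 df with baseline and centre

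For ρ = 0.5: ρ²k = 0.1215; outcome SD = 2√0.8715 = 1.87; residual SD = 2√0.75 = 1.73; ρ*² = 0.1215/0.8715 = 0.139, so ρ* = 0.37; equivalent N = 60/0.861 = 70.

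| ρ assumed | ρ* enrolled | SD unadjusted / ANCOVA | Equivalent N | CI half-width, points | Power, 1 point |
|---|---|---|---|---|---|
| 0.3 | 0.21 | 1.95 / 1.91 | 63 | 1.01 → 0.99 | 50% → 51% |
| 0.5 | 0.37 | 1.87 / 1.73 | 70 | 0.97 → 0.90 | 53% → 59% |
| 0.7 | 0.56 | 1.73 / 1.43 | 88 | 0.89 → 0.74 | 60% → 76% |

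**5. Cost.** The critical t moves from 2.002 (58 df) to 2.003 (56 df). If baseline were useless (ρ = 0), power at a 0.5 SD effect would go from 47.8% to 47.7%.

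**6. Change scores as the comparator.** Their variance is 4[(1 − ρ)²k + 1 − ρ²], giving SDs of 2.14, 1.87 and 1.49 and power of 43%, 53% and 73%. ANCOVA gives 51%, 59% and 76%.

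**7. Simulation of the distribution-based choice and of centre.** Each of 5,000 runs per scenario used integer NRS from 0 to 10, baseline of at least 4 and 15/15 per centre. A Shapiro test chose between t and Mann-Whitney.
- With no effect, type I error was 4.3% to 4.5% for the chosen test and 4.4% to 4.9% for ANCOVA.
- With a 1-point effect and nominal ρ = 0.5, power was 50% for the chosen test and 57% for ANCOVA.
- With a 1-point difference between centres added, power was 47% and 57%.

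**The case against.** **Covariates and model form are commonly left to the SAP, which is not shown.** This stands as far as baseline NRS is concerned. A reader might infer that the protocol rules out baseline adjustment, but it only fails to mention it. Within-group change over time also uses baseline in some form. The other elements are stated text: a test that depends on the distribution, centre placed under sensitivity analyses, and two contrasts without a rank. The choice of time is left open for an endpoint that section 10.1 calls the only primary one.

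**Choosing the test from the data might be thought to inflate the false-positive rate.** For a preset normality rule the simulation shows no inflation. What remains is that the protocol presets no rule, and that the quantity estimated changes with the test.

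**Ignoring a balanced factor does not bias the comparison.** Correct. It costs precision, and the cost is modest: about 3 percentage points of power (50% to 47%) for a 1-point centre difference.

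**The superiority wording already points to the between-arm contrast.** This is fair, and nothing in section 10.1 makes within-arm change an efficacy test. It also does not call within-arm change descriptive. A figure for regression to the mean cannot be supported. It would treat the screening score as the baseline score, whereas questionnaires start at the first treatment visit and the entry criterion concerns daily pain.

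**The last-visit NRS might be read as preceding the eighth session,** because section 3 says "Relevant questionnaires will be sent before each visit". The documents do not settle this. The Summary has questionnaires filled in during the visits, and the flowchart of measurements is a figure not available here.

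**Conclusion.** The point holds as a recommended improvement. Section 10.1 leaves the statistic, the time and the leading contrast of its primary pain analysis open, and it keeps a factor used in allocation out of the main analysis. A prespecified ANCOVA at one time is better and uses data already planned.

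The size of the gain is uncertain because the correlation is assumed. It is negligible at 0.3 (about 3 patients' worth), modest at 0.5 (about 10) and substantial at 0.7 (about 28). A reader might apply 1 − ρ² to an unrestricted correlation and obtain a larger gain, but that ignores the NRS entry threshold. The figures here treat the entry score as the baseline. If baseline is a separate reading, the restriction is somewhat weaker and the gain somewhat larger. The figures also assume no centre difference, complete baseline data and no dropout. Against change scores, the gain at 0.7 is smaller (73% to 76%).

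The case for fixing the method does not depend on these figures: one defined estimand at one defined time is needed at any correlation. The documents do not support a claim of type I error inflation from a preset normality rule, of bias from omitting centre, or of a deliberate exclusion of baseline adjustment.

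**What to change.** Replace the NRS sentences in section 10.1 with wording such as: *The primary analysis is the between-arm difference in NRS at [one named time], estimated by ANCOVA with baseline NRS and centre as covariates, with a 95% confidence interval and a two-sided 5% test. NRS at the other time is analysed in the same way as a secondary outcome. A rank-based analysis is a sensitivity analysis. Within-arm changes are descriptive.*

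The sponsor should choose between the last treatment visit and six weeks, since nothing in the protocol favours either, and repeat the choice in section 8.1.1. The same sentence should say which reading is the baseline. Only covariates measured before treatment should enter the primary model, because HADS or pain medication recorded later could be affected by treatment.

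The cost is protocol wording and 2 degrees of freedom. No extra patients or measurements are needed, but baseline NRS must be complete.

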#### **8.4 Withdrawal of individual subjects**

Subjects can leave the study at any time for any reason if they wish to do so without any consequences. The investigator can decide to withdraw a subject from the study for urgent medical reasons.

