#### **8.5 Replacement of individual subjects after withdrawal**

We follow an 'intention to treat' strategy and have no intention to replace subjects after withdrawal.

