**8.6 Follow-up of subjects withdrawn from treatment**

Not applicable.

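### Section 10.1 gives the primary pain comparison two analysis sets, intention-to-treat and per protocol, without saying which is primary, and section 8.6 plans no follow-up for patients who stop treatment

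*Protocol*

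**What the plan says.** Protocol section 10.1, Objective 2, names NRS pain as the one primary endpoint and plans a superiority test at two-sided 0.05. On the analysis set it says: "Changes within the treatment groups over time as well as differences between groups will be assessed by intention-to-treat analyses". The next sentence is: "Also the primary analysis will follow the per protocol principle". The sensitivity analyses listed after that concern centre, HADS and pain medication. None compares analysis sets.

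Section 8.5 says: "We follow an 'intention to treat' strategy and have no intention to replace subjects after withdrawal".

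Section 8.4 provides that "Subjects can leave the study at any time for any reason if they wish to do so without any consequences". Section 8.6, headed "Follow-up of subjects withdrawn from treatment", is answered only as not applicable. Section 3 (Study design) says that "all patients in both groups will undergo all the measurements", without mentioning patients who stop the sessions.

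Section 4.4 sets 30 patients per arm and explains that no pilot data on pain exist. The protocol gives no SD, effect size or expected stopping rate.

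**The concern.** Two adjoining sentences point the primary comparison at different sets of patients. Intention-to-treat keeps everyone in the arm to which they were randomised. Per protocol keeps a subset defined by what happened after randomisation. The words *the primary analysis* are attached to the second, while section 8.5 supports the first. Any later analysis plan would have to choose, and nothing in the protocol tells it how.

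Two things are at stake. First, in a superiority trial a per-protocol comparison loses the protection of randomisation when the patients removed differ between arms in number or in prognosis. Second, if the order is not fixed before unblinding, the headline result can be chosen after both have been seen. Section 4.4 says further trials may be built on these results, so a biased effect estimate would carry forward into their design.

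Section 8.6 bears on the same point. Intention-to-treat is only as good as the outcomes collected from patients who stop, and the section written for those patients plans nothing.

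**Working it through.** **1. The statements side by side**

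| Place in the protocol | Set for the between-group pain comparison |
|---|---|
| 10.1, Objective 2, first statement | Intention-to-treat |
| 10.1, Objective 2, next sentence | Per protocol, attached to the primary analysis |
| 8.5 | Intention-to-treat, no replacement |
| 10.1, sensitivity analyses | Centre, HADS, pain medication; analysis set not listed |

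No sentence ranks the two sets.

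**2. Plan's own figures.** Section 8.2 gives 15 per arm in each of two centres: 2 × 15 = 30 per arm, 60 in total, which agrees with section 4.4. There is no power calculation to reproduce.

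**3. What a per-protocol primary analysis could do.** All inputs except the 30 per arm are assumptions: no true effect, NRS SD 2, a proportion p₁ stopping on active and p₀ on placebo, and stoppers d points worse than non-stoppers in both arms.

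With no true effect both arms have the same overall mean μ. Within an arm, μ = (mean of non-stoppers) + p × d, so the non-stoppers' mean is μ − p × d. Hence

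- bias in favour of HALF-MIS = (p₁ − p₀) × d
- SE = 2 × √(1/n₁ + 1/n₀), with n₁ = 30(1 − p₁) and n₀ = 30(1 − p₀)
- probability of a false claim for HALF-MIS = 1 − Φ(1.96 − bias/SE), which is 2.5% when the bias is zero

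Worked case, 20% against 5% and d = 1.5: bias = 0.15 × 1.5 = 0.225; n₁ = 24, n₀ = 28.5; SE = 2 × √(1/24 + 1/28.5) = 0.554; bias/SE = 0.406; probability = 1 − Φ(1.554) = 6.0%.

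All corners of active 15-20%, placebo 5-10%, d 1.5-2:

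| Active / placebo stopping | d | Bias (NRS points) | SE | False claim for HALF-MIS |
|---|---|---|---|---|
| 15% / 10% | 1.5 | 0.075 | 0.552 | 3.4% |
| 15% / 10% | 2 | 0.10 | 0.552 | 3.8% |
| 20% / 10% | 1.5 | 0.15 | 0.561 | 4.5% |
| 15% / 5% | 1.5 | 0.15 | 0.545 | 4.6% |
| 20% / 10% | 2 | 0.20 | 0.561 | 5.4% |
| 15% / 5% | 2 | 0.20 | 0.545 | 5.6% |
| 20% / 5% | 1.5 | 0.225 | 0.554 | 6.0% |
| 20% / 5% | 2 | 0.30 | 0.554 | 7.8% |

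The range is 0.075-0.30 points and 3.4%-7.8%.

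**4. Direction.** With equal rates and equal deficits, (p₁ − p₀) × d = 0. With the rates of the worked case swapped (5% active, 20% placebo, d = 1.5), the bias is −0.225, against HALF-MIS, and a false claim in its favour falls to 1 − Φ(1.96 + 0.406) = 0.9%.

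**5. A second illustration on other assumptions.** This simulated a t-test with 30 per arm and no true effect (40,000 runs per scenario). Stopping was equally frequent in both arms but correlated with a worse outcome in the active arm only. The two-sided per-protocol error was 0.057-0.079 at 10% stopping, 0.064-0.141 at 20% and 0.076-0.213 at 30% (correlation 0.3 to 0.7). When stopping was unrelated to outcome it stayed at about 0.05. Intention-to-treat with complete outcomes stayed at about 0.05 throughout. Equal stopping rates alone therefore do not protect the per-protocol comparison.

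**The case against.** **The word *Also*.** It can be read as adding a per-protocol analysis of the primary endpoint beside the intention-to-treat one, and section 8.5 supports that. This is a fair reading and may be what was meant. It leaves the two sets unranked, however, and the sentence still attaches per protocol to the primary analysis. What stands of the objection is that the defect is a missing order, and that per protocol as the sole primary set is only one reading.

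**Section 8.6.** A reader might infer that assessments end when sessions end, so that the intention-to-treat set shrinks to completers. The protocol does not say that. Many template headings are answered as not applicable, section 8.4 speaks of leaving the study and not of stopping sessions, section 3 says all patients undergo all measurements, and the flowchart is not shown. The supportable point is that 8.6 sits badly with intention-to-treat and with section 3.

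**Direction of the bias.** A reader might infer that the protocol expects this device to cause dizziness and nausea, so that dropping stoppers must favour HALF-MIS. The summary and section 5.1 report those symptoms from some earlier trials and say they pass after the session. Section 1 says most people find the stimulation pleasant and only a few do not. The control arm also feels vibration. Placebo patients might equally stop for lack of relief, which would reverse the bias.

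**Two chances of significance.** Two unranked sets do offer a choice, but they overlap heavily and their tests are strongly correlated. The inflation from that source would be well below that of two independent tests and is not quantified here.

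**SAP and pilot status.** An SAP may properly hold the definition of the per-protocol set and the handling of missing data; neither is criticised. It cannot follow both statements about the primary analysis. Pilot status lowers the consequence, but a superiority test at 0.05 is still planned.

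**Conclusion.** The point holds as a missing hierarchy: the protocol names two analysis sets for its primary superiority test, ranks neither, and allows a reading in which per protocol is primary. This rests on the text alone.

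The size is illustrative. If per protocol were primary and active patients stopped more often, the assumed inputs give a bias of 0.075-0.30 NRS points and a false-claim rate for HALF-MIS of 3.4%-7.8% against 2.5%. SD, stopping rates and deficit are all assumed, so these figures show what is possible and do not predict this trial. They describe per protocol as the sole primary set, not the effect of choosing between two sets.

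Section 8.6 is a related weakness and needs reconciling with 8.5 and section 3. Should be fixed; it is not critical in a 60-patient pilot.

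**What to change.** In section 10.1, replace the per-protocol sentence with wording such as: *The primary analysis of NRS pain includes all randomised patients in the arm to which they were randomised. A per-protocol analysis will be reported as a supportive sensitivity analysis.*

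In section 8.6, replace the present entry with: *Patients who stop the sessions but do not withdraw consent are asked to complete the end-of-treatment and six-week outcome assessments as scheduled.*

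Both changes should be in place before unblinding. The cost is two pieces of protocol wording, notified to the ethics committee as an amendment, plus already planned assessments for the few patients who stop early. Treatment and sample size are unchanged.

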### 10.2 Secondary study parameter(s)

Secondary endpoints are the PDI and EQ-5D-3L (objective 2) and CSI (objective 3). They will be analyzed exploratory at a two-sided significance level of 5%. The HADS will be used to control for depression as an important confounder, because depression has been hypothesized to change alongside with the chronic pain condition.

### 10.3 Other study parameters

Descriptive statistics (such as demographics, duration and type of pain and comorbidities): data will be presented as means  $\pm$  standard deviation or medians  $\pm$  interquartile ranges.

